#### 2.1.2. Primary Efficacy Endpoint

The Functional Independence Measure (FIM; lasting 30–45 min) (time frame: Changes from baseline to week 22; changes from week 22 to week 48) is an 18-item 7-point Likert scale evaluating physical, psychological, and social function, indicating the amount of assistance required for each task. A final total score is obtained ranging from 18 (complete dependence/total assistance) to 126 (complete independence) [37].

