#### 2.1.1. The Study’s Protocol

The protocol’s shape relies on our own clinical experience over the last decade [6,7,8,9,10,11,12,13,35]. The hippotherapy approach will comprise three cycles. The first one consists of two-week daily sessions. This first phase aims to (i) evaluate the patient’s neuro-functional capacities, and (ii) build the initial treatment taking into account the silent barriers that may exist (e.g., PTSD, fatigue, pain, and fear) and that strongly interfere with the individual’s functional outcome [36] developing ways to overcome them. After a nine-week “hippotherapy wash out” period during which the patient continues with the conventional neurorehabilitation care, an intermediate one-week daily hippotherapy cycle followed. Then, after a second nine-week “hippotherapy wash out” period, a final one-week daily hippotherapy cycle will occur. The conventional outpatient rehabilitation for each patient in the hippotherapy group will be temporarily suspended during the hippotherapy cycles. Six months after the end of the rehabilitation protocol, patients will be monitored for sustainability of functional gains. The entire protocol will last 48 weeks (see Figure 1).

The so-called “hippotherapy wash out” period has three main objectives: fixing of the new schemes; translating them to day-to-day skills; and revealing new unmet needs. Our current clinical practice supports the proposed rhythm for rehabilitation through hippotherapy (see Section 2.3.3).

A battery of validated tests are used to study the patient’s level of disability, sensorimotor function, and quality of life. A measurement of the quality of life and burden of caregivers is also included. Patients will undergo evaluations prior and at the end of the neurorehabilitation program, as well as six months after the end of the neurorehabilitation program (end of the study).

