#### 2.1.4. Sample Size and Recruitment

From the related data [47], the sample-size calculation was based on a minimum reasonably significant difference in the primary outcome (Functional Independence Measure) of 22 points with a standard deviation of σ = 28.43 [48]. To detect that difference with a power of 80% using a two-sample *t*-test at a two-sided significance level of 5%, a total of 44 patients in the randomized arms (22 per arm) will be required. We will recruit 52 patients into the study, to allow for an attrition rate of around 20%.

Recruitment will be conducted during a 12-month period. The study will end when the last patient enrolled undergoes a neurological evaluation to determine the durability of functional recovery.

The end-of-treatment assessment will be completed within two weeks of the end of 22 weeks of treatment and the end-of-protocol assessment will be completed 26 weeks after the end of treatment. The protocol began in the fourth quarter of 2021 and will run through the third quarter of 2024.

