#### 2.4.2. Statistical Analysis

Statistical methods will be in accordance with the CONSORT statement for reporting of randomized trials. Appropriate non-parametric statistics will be used to evaluate the comparability of the intervention and control group at baseline in terms of the clinical characteristics. If, despite the stratified randomization procedure, the groups are not comparable for one or more background variables, those variables will be routinely employed as covariates in the subsequent analyses. The scores for each variable (primary and secondary endpoints) will be calculated according to the published scoring algorithms. Intergroup (effect of the treatment on the measured variable, compared to the control) and intragroup (evolution of the measured variable on the same group) differences in the mean scores over time will be tested using a multilevel analysis. The effect sizes will be calculated using standard statistical procedures. All analyses will be conducted on an ITT basis. PP analyses will also be carried out (as secondary analyses). To test the effectiveness of hippotherapy intervention on functional independence (FIM; primary outcome), non-parametric ANOVA measures for non-linear scores (Friedman’s test for paired data) will be conducted. In addition, to test the effectiveness of the intervention on the secondary outcome variables, including the caregivers’ measurements, non-parametric ANOVA procedures (Friedman’s test for paired data) will also be applied. Post hoc analyses (e.g., additional correlation and covariance statistical procedures) will be conducted according to the obtained results. They will fine-tune the initial data analysis by taking into account potential confounding factors. Given the power of the study (80%), the post hoc results will be statistically robust and therefore reliable. The threshold of statistical significance will be *p* = 0.05. The statistical analyses will be implemented by the CRO using SAS^®^ software (version 9.4, SAS Institute, Cary, NC, USA).

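### The primary FIM endpoint has two unranked time frames, and the second (week 22 to week 48) starts after treatment, so on its own it cannot show that a benefit was sustained

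*Protocol article*

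**What the plan says.** Section 2.1.2 of the protocol article gives the time frames of the single primary endpoint, the FIM, as "Changes from baseline to week 22; changes from week 22 to week 48". It does not rank them. Section 2.1.3 uses the same pair for mRS and patient SF-36. The other secondary measures run only from baseline to week 22.

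The visits are fixed in Section 2.1.4. The first follow-up visit comes when the 22-week programme closes, with a two-week window. For the last visit the text reads "the end-of-protocol assessment will be completed 26 weeks after the end of treatment", which is week 22 + 26 = week 48. Section 2.1.1 gives the purpose of the late visit: "patients will be monitored for sustainability of functional gains". Section 2.1.4 likewise ties the end of the study to an assessment of how durable the recovery is.

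The sample size in Section 2.1.4 rests on one difference, "of 22 points with a standard deviation of σ = 28.43", tested by a two-sample t-test "at a two-sided significance level of 5" per cent and "with a power of 80" per cent. It does not say which of the two changes the 22 points describe.

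Section 2.4.2 plans a multilevel analysis of differences between and within groups over time, and Friedman's test for the FIM. Neither is tied to a named visit or between-arm contrast. One general rule follows: "The threshold of statistical significance will be" p = 0.05.

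**The concern.** A primary endpoint should be one quantity whose result decides the trial. Here there are two, and a reader of the final report could not tell from this document which one was meant to decide.

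The second quantity also does not match its purpose. A change measured from the end of treatment takes the treated arm's gain as its new zero, so a treatment that works and lasts looks the same on it as one that never worked. A non-significant week 22-48 result could then be presented as gains maintained when it shows nothing of the kind by itself. If instead the gain fades, the same contrast favours the control arm although neither arm is ahead at week 48.

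**Working it through.** **The plan's own sample size.** The inputs are difference 22, SD 28.43, 80% power and two-sided 5%, all from Section 2.1.4.
- Normal approximation: n per arm = 2 × (1.960 + 0.842)² × 28.43² / 22² = 2 × 7.849 × 1.670 = 26.2, so 27 per arm. The exact t calculation gives 28.
- The stated 22 per arm is not reproduced. It appears only with a one-sided 5% test (21 by the normal approximation, 22 by t).
- That mismatch is a separate matter. What counts here is that the calculation covers one comparison, not two.

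**What each contrast measures.** Let D22 and D48 be the true between-arm FIM differences (hippotherapy minus control) at weeks 22 and 48. Randomisation makes the expected baseline difference 0. The between-arm differences in change are then:
- baseline to week 22: D22
- week 22 to week 48: D48 - D22
- baseline to week 48: D48

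With the plan's 22 points:

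| Scenario | D22 | D48 | Baseline-22 | 22-48 | Baseline-48 |
|---|---|---|---|---|---|
| Benefit fully kept | 22 | 22 | 22 | 0 | 22 |
| Never any benefit | 0 | 0 | 0 | 0 | 0 |
| Benefit fully lost | 22 | 0 | 22 | -22 | 0 |

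The 22-48 column does not separate the first row from the second. The last column does. This step needs no assumption beyond the 22 points.

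**How often each contrast would be significant.** This was simulated with 22 per arm, SD 28.43 at every visit, two-sample t-tests at two-sided 5% and 20,000 trials per setting. The between-visit correlation is assumed to be equal for all pairs of visits.

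| Scenario | Result counted | Corr. 0.5 | Corr. 0.7 | Corr. 0.9 |
|---|---|---|---|---|
| Fully kept | 22-48 favours hippotherapy | 2.7% | 2.4% | 2.5% |
| Fully kept | Baseline-48 favours hippotherapy | 70.5% | 90.0% | >99% |
| Fully lost | 22-48 favours control | 70.2% | 90.3% | >99% |

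**Error rate if both changes are tested.** Suppose each change is tested between arms at two-sided 0.05 and either may carry the claim.
- Independent tests: 1 - 0.95² = 0.0975.
- With equal SDs and equal visit correlations r, the two changes share the week-22 value. Their covariance is -(1 - r)σ² and each variance is 2(1 - r)σ², so their correlation is -0.5 whatever r is. The bivariate normal calculation then gives 0.0907.
- At a correlation of ±0.8 it is 0.078.

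The simulated no-effect trials gave 8.9% to 9.4%. All these figures count false positives in either direction.

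**The case against.** Two stronger readings are tempting, and the document does not support either.

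The first is that the plan cannot show sustained benefit at all. It can. The two changes add up to the baseline-to-week-48 change, FIM is measured at all three visits, and the multilevel analysis in Section 2.4.2 could estimate the week-48 difference. Read together, a positive first change and a flat second one do point to retention. What stands is narrower: the contrast that answers the question is not named, and the one that is named is uninformative when read alone.

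The second is that the plan runs two primary tests at 0.05 and so has an inflated error rate. Section 2.4.2 gives one general threshold and does not describe two separate between-arm tests. The two-sample t-test appears only in the sample-size text. A test order or alpha split may sit in the analysis plan, which is not shown, and its absence from an article is not a fault. The error figures are therefore conditional.

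A test order, however, would not mend the second contrast. Nor would a rule that both changes must succeed: a benefit that is fully kept passes the second test in only about 2.5% of trials. A Bonferroni split at 0.025 each, with 22 points and SD 28.43 assumed for both, needs 32 per arm (normal) or 34 (t). At 22 per arm it leaves power of 0.63 or 0.60 per test.

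It is also fair to say that change after treatment is a reasonable description of decay. The fault lies in giving it primary status, not in reporting it.

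**Conclusion.** The point holds in this form. The article places two FIM changes under one primary endpoint without ranking them, and sizes the trial for a single 22-point difference that it attaches to neither. The second change, taken alone, has an expected between-arm difference of 0 under both full success and complete failure, and of -22 when the arms end level. The week-48 between-arm difference relative to baseline is named nowhere for FIM, mRS or patient SF-36, although sustainability is a stated aim.

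The scenario arithmetic rests only on the plan's own 22 points. The simulated percentages rest on assumed visit correlations. The 9.1% to 9.75% error rate further assumes two separate tests, either of which may carry the claim, with no order or split set in the analysis plan. No passage says that a null second change would be reported as sustained gain. That is a risk the wording leaves open, not something the document states.

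**What to change.** - **Primary:** name the between-arm difference in FIM at week 22, adjusted for baseline, as the single primary endpoint, since this is the end of the treatment period. State in Section 2.1.4 that the 22 points refer to it.
- **Key secondary:** replace the week 22-48 FIM change by the between-arm difference at week 48, adjusted for baseline, tested at 5% only if week 22 is significant.
- **Description:** keep the week 22-48 change by arm, without a confirmatory test.
- **mRS and patient SF-36:** replace the week 22-48 change by the baseline-adjusted week-48 difference. Both stay secondary.

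Other arrangements could also control the error, but whichever is chosen should include the week-48 contrast.

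The cost is an amendment to the protocol, the registry entry and the analysis plan, with no new visits or data. It changes the primary endpoint of a trial that began in late 2021, so it must be made and dated before any outcome is compared by arm. The gate has a price too: a benefit seen only at week 48 could not be claimed as confirmed.

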#### 2.1.3. Secondary Efficacy Endpoint

For the patient:

The modified Rankin Scale (mRS; lasting 5–15 min) (time frame: Changes from baseline to week 22; changes from week 22 to week 48) is a standardized measure that describes the extent of disability after stroke. The mRS is a single-item scale. It ranges from 0 (no symptoms) to 6 (death due to stroke) [38,39].

The Fugl-Meyer Assessment (FMA; lasting 30–35 min) (time frame: Changes from baseline to week 22) is a stroke-specific, performance-based impairment/recovery index. It is designed to assess motor functioning, balance, sensation, and joint functioning in stroke patients. Assessment items are scored based on the ability to complete the item using a 3-point Likert scale (0 = cannot accomplish; 1 = partially accomplished; and 2 = completely accomplished) where very severe ranges from 0–35, severe 36–55, moderate 56–79, and light > 79 (max. score 226) [40].

The Berg Balance Scale (BBS; lasting 10–15 min) (time frame: Changes from baseline to week 22) is a 14-item 4-point Likert scale where patients must maintain positions and complete moving tasks of varying difficulty. A global score is calculated out of 56, which represents the ability to independently complete the test [41,42].

The walking distance in 2 min (2-MWT; lasting less than 5 min) (time frame: Changes from baseline to week 22) reports the walking distance of the patient after 2 min. The number and duration of rests during the 2 min are also measured [43].

The Short-Form Health Survey (SF-36; lasting 10 min) (time frame: Changes from baseline to week 22; changes from week 22 to week 48) is a 36-item weighted Likert scale questionnaire, which measures quality of life (QoL) on 8 domains, both physically and emotionally based. The SF-36 is a generic patient-report measure used inter alia in stroke [44].

For the caregiver:

The Short-Form Health Survey (SF-36) for quality of life (time frame: Changes from baseline to week 22)—see above.

The Zarit Burden Inventory (ZBI; lasting 30 min) (time frame: Changes from baseline to week 22) is a 22-item 5-point Likert scale. The higher the score, the more extensive the burden. It is one of the most used instruments to assess caregiving burden in clinical and research settings [45,46].

#### 2.1.4. Sample Size and Recruitment

From the related data [47], the sample-size calculation was based on a minimum reasonably significant difference in the primary outcome (Functional Independence Measure) of 22 points with a standard deviation of σ = 28.43 [48]. To detect that difference with a power of 80% using a two-sample *t*-test at a two-sided significance level of 5%, a total of 44 patients in the randomized arms (22 per arm) will be required. We will recruit 52 patients into the study, to allow for an attrition rate of around 20%.

Recruitment will be conducted during a 12-month period. The study will end when the last patient enrolled undergoes a neurological evaluation to determine the durability of functional recovery.

The end-of-treatment assessment will be completed within two weeks of the end of 22 weeks of treatment and the end-of-protocol assessment will be completed 26 weeks after the end of treatment. The protocol began in the fourth quarter of 2021 and will run through the third quarter of 2024.

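### Recruiting 52 patients covers about 15% attrition, not the stated 20% or so: a 20% loss leaves 41–42 evaluable against the required 44

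*Protocol article*

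**What the plan says.** Section 2.1.4 (Sample Size and Recruitment) builds the sample size in two steps.

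- **Evaluable number.** The target is a "minimum reasonably significant difference in the primary outcome (Functional Independence Measure) of 22 points", "with a standard deviation of σ = 28.43". For 80% power with a two-sample t-test "at a two-sided significance level of 5" per cent, the article concludes that "a total of 44 patients in the randomized arms (22 per arm) will be required".
- **Attrition allowance.** "We will recruit 52 patients into the study, to allow for an attrition rate of around 20" per cent.

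The section gives no formula for the second step. It does not say that the 44 already contains an allowance for loss, nor whether the 20% refers to loss by week 22 or by week 48.

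**The concern.** Attrition is a fraction of those recruited. To end with 44 after losing a fraction *a*, one recruits 44/(1 − *a*). At *a* = 0.20 that is more than 52, so the three stated figures (44 required, 52 recruited, around 20% lost) cannot all hold.

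At stake is whether the trial reaches its own evaluable number at the attrition it expects, and how much power goes with the shortfall. The power figure is also used elsewhere: Section 2.4.2 cites 80% power as the reason for trusting the post hoc results.

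**Working it through.** **Inputs**, all from Section 2.1.4: 44 required (22 per arm), 52 recruited, attrition around 20%, difference 22 FIM points, SD 28.43, two-sample t-test, two-sided 5%, claimed power 80%.

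**1. How 52 can be reached.**
- Division at 20%: 44/0.80 = 55. By arm, 22/0.80 = 27.5, rounded up to 28, so 56 in total. Neither is 52.
- Mark-up at 20%: 44 × 1.20 = 52.8. This is close to 52, although it rounds to 53.
- Division at 15%: 44/0.85 = 51.8, which rounds to 52.

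The eight added patients are 8/44 = 18.2% of 44 and 8/52 = 15.4% of 52. The figures are consistent with a mark-up on 44 rather than division by 0.8.

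**2. What 52 leaves at different attrition rates.**

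| Attrition | Evaluable = 52 × (1 − a) |
|---|---|
| 15% | 44.2 |
| 16% | 43.7 |
| 18% | 42.6 |
| 20% | 41.6 |

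The break-even rate is 1 − 44/52 = 15.4%.

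**3. Power from the stated inputs.** The standardised difference is d = 22/28.43 = 0.774. The noncentrality is d × √(n₁n₂/(n₁+n₂)), and power comes from the noncentral t-distribution on n₁ + n₂ − 2 degrees of freedom, two-sided 5%.

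| Evaluable (per arm) | Noncentrality | Power |
|---|---|---|
| 44 (22/22) | 0.774 × √11 = 2.57 | 70.8% |
| 42 (21/21) | 0.774 × √10.5 = 2.51 | 68.7% |
| 41 (21/20) | 0.774 × √10.24 = 2.48 | 67.6% |
| 52 (26/26, no loss) | 0.774 × √13 = 2.79 | 78.1% |

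**4. Splitting the gap to 80%.**
- Due to the 44: 80 − 70.8 = 9.2 points.
- Due to the attrition step: 70.8 − 68.7 = 2.1 points at 42 evaluable, or 70.8 − 67.6 = 3.2 points at 41.

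**5. The 44 is a separate matter.** Solving the stated two-sided t-test for 80% power gives 27.2 per arm, so 28 per arm or 56 evaluable. A one-sided 5% t-test gives 21.4, rounded up to 22 per arm, but the article states a two-sided test.

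**The case against.** - **The article says only around 20%, and the shortfall is small.** The looseness does not rescue the figure, because 16% attrition already leaves fewer than 44. The point about size stands: the shortfall is two or three evaluable patients and 2–3 points of power.
- **The fall from 80% to about 69% might be put down to this slip.** A reader might infer that, but the stated inputs do not support it. Reaching 44 exactly would still give only about 71%, and all 52 evaluable would give 78.1%. Most of the gap belongs to the 44.
- **The allowance might be taken as certainly computed as 44 × 1.2.** The article shows no formula, and 52.8 does not round to 52. A mark-up is a plausible origin and no more. The inconsistency stands whatever its source.
- **The timing of the 20% is not stated.** The primary endpoint in Section 2.1.2 has two time frames, baseline to week 22 and week 22 to week 48. If the 20% is loss by week 48, more than 41–42 patients could be evaluable at week 22. This stands, and the evaluable figure is conditional on it.
- **An article condenses a fuller protocol.** That would excuse an omission. Here the article prints three figures that disagree with one another.

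**Conclusion.** The attrition statement in Section 2.1.4 is wrong as written. Recruiting 52 covers 15.4% attrition for 44 evaluable patients. At 20% it leaves 41–42, and keeping 44 would take 55 (56 for equal arms). Under the stated inputs the slip lowers two-sided t-test power from about 71% to about 68–69%.

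This assumes that the full 20% is lost by the analysis in question, that losses are spread about evenly over the arms, and that lost patients contribute nothing to an unadjusted t-test.

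Two stronger conclusions do not follow. The slip does not explain the whole distance from 80%. Nor would recruiting 55 or 56 restore 80% power, since the 44 falls short on its own inputs.

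**What to change.** In Section 2.1.4, state that 52 recruited covers about 15% attrition for 44 evaluable patients, and that 20% attrition leaves about 42 evaluable with about 69% power for the stated t-test, against about 71% at 44. Say at which visit the attrition is counted.

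Make this change together with the correction of the 80% power claim for 44. Restating the allowance as 15% on its own would leave that claim in place. The 80% figure repeated in Section 2.4.2 should follow the corrected one.

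The cost is a few restated figures. No change in recruitment is needed for this correction.

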### 2.2. Selection/Treatment of Subjects

#### 2.2.1. Participants

Participation in the study will be proposed to every patient hospitalized at the CHSF after a stroke, fulfilling the inclusion criteria. Patients will be drawn at random to build the two arms of the study. The study participants will be adult males or females with a moderate to severe disability (Rankin score ≥ 3 and ≤4 at baseline). Each participant will present written informed consent in accordance with the Declaration of Helsinki. The data will be anonymized and properly stored to respect the confidentiality of sensitive medical data and EU GDPR legislation. Those responsible for the selection and inclusion of patients are the neurologists of the Neurology Service and Neurovascular Unit of the CHSF coordinated by [name], head of department and principal investigator. A certificate of non-contraindication to hippotherapy will be established by the neurologists of the CHSF for each single patient. In case of a patient’s withdrawal, he/she will continue to benefit the planned care with no impact on its quality.

